## Methods and analysis

This study protocol was designed according to the Standard Protocol Items: Recommendations for Interventional Trials (SPIRIT) checklist (19), with adaptations based on the recommendations outlined by Thabane and Lancaster (20).

### Study design and setting

The PĒPI ARC study is a prospective, non-randomised, feasibility study that uses a mixed methods approach to evaluate the previously outlined domains of feasibility. The study will run from March 2023 to September 2024, with the primary time point being at the completion of the PĒPI ARC Hub trial period. The study setting will be a regional Hub based in Wellington to allow follow-up of eligible infants who received care at the Wellington NICU. The PĒPI ARC Hub will be delivered using two components: a community-based, multidisciplinary face-to-face diagnostic clinic in Wellington and a virtual Hub to support regional CP-specific neurodevelopmental follow-up, education, and information sharing and foster relationships among the Wellington team, local community, and regional child development services (CDS) and paediatricians.

The Wellington NICU is a tertiary unit that provides perinatal and surgical care for infants from Wellington and seven regional referral centres from half of the North Island and the top of the South Island of NZ. The unit cares for a third of all infants admitted to a tertiary NICU in NZ. It is estimated that between 100 and 120 infants per year will fit the criteria for the CPCN Recommendations pathway, of which approximately 30% live in the Wellington area (21) (i.e., to be invited to attend the in-person clinic), and the remainder will receive follow-up in their local regions (supported by the PĒPI ARC team through telehealth).

For the Wellington NICU catchment area, data from the NZ CP Register (2009–2020) showed that 17% of infants received a diagnosis of CP before 6 months of age and 34% before 12 months (22).

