## Introduction

In Aotearoa New Zealand (NZ), it is estimated that every 3 days a baby is born who will later receive a diagnosis of Hōkai Nukurangi, the Te Reo Māori term for cerebral palsy (CP) (1). Of these babies, approximately 60% are diagnosed after 12 months of age, with a reported median age of CP diagnosis at 17 months of age in NZ (1). Many families of children with CP living in NZ perceive diagnosis delays, with nearly 20% of them reporting delays of more than 12 months (2).

Historically, CP has been diagnosed using a combination of clinical and neurological signs, which often do not appear until the child is older. In 2017, an international evidenced-based guideline was published for accurate and early CP diagnosis using a combination of different assessment tools (3). Through a combination of brain Magnetic Resonance Imaging (MRI), the Prechtl General Movements Assessment (GMA) (4), and the Hammersmith Infant Neurological Examination (HINE) (5), infants with detectable newborn risk factors for CP can now be diagnosed as early as 3 months of age (corrected for prematurity) with a sensitivity and specificity of 97% and 99%, respectively, in a retrospective case–control study (6). The successful implementation of these recommendations has seen significant reductions in the age of identifying “high risk of CP” [e.g., in an Australian clinic with an average age of 4.4 months (7)] and the average age of CP diagnosis [e.g., in a US clinic from 18 months prior to implementation down to 12 months (8), in a network of US clinics 19.5 months to 9.5 months (9), and in an Australian clinic to 8.5 months (7)].

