### Hypotheses

**H1**: Equivalent levels of infants who meet the criteria will undergo assessments with CP-specific diagnostic tools outlined in the CPCN Recommendations, independent of region of residence or ethnicity.

**H2**: Whānau and health professionals will find the PĒPI ARC Hub model of care acceptable (over the acceptability constructs).

**H3**: The demand will be high with infants who meet the criteria choosing to enroll in the PĒPI ARC study over standard care.

**H4**: More than 34% of infants with CP will be diagnosed before 12 months of corrected gestation age (CGA) and >17% before the age of 6 months CGA.

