#### Infants and parents/caregivers

Infants must meet the following eligibility criteria:
i.admitted to the NICU at Wellington Regional Hospital within the study period,ii.have a discharge address located within the Wellington region or within one of the referral regions of the Wellington NICU, andiii.and meet the criteria of the CPCN Recommendations for newborn detectable risks for CP (Table 1).Infants will be excluded if they are born with a life-limiting condition and not expected to survive past the first year of life or if the family is expected to move out of the catchment area before the infant is 3 months CGA.

Infants and their parents/caregivers will be invited to participate in the study by a member of the PĒPI ARC research team (not directly involved in providing healthcare for the infant in the NICU). Recruitment can occur at any point during the NICU admission prior to discharge. Support from social workers and Whānau Care Services is available to assist with recruitment decision-making, and parents are encouraged to discuss and seek support from their extended family. Families will be advised that they can instead choose the usual care option (see below).

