## Discussion

This paper details the protocol for a feasibility study to ascertain if a multidisciplinary regional Hub, namely, PĒPI ARC, can support the equitable implementation of the NZ CPCN *Best Practice Recommendations for Early Detection of CP, Intervention, and Monitoring* for infants with newborn detectable risks. Feasibility will be assessed for acceptability and demand among families and health professionals and for efficacy in relation to reducing the age of CP diagnosis and improving experiences around communication and information sharing between families and health professionals.

The study is limited to only infants with newborn detectable risk factors for CP who are admitted to the Wellington NICU and who either live in Wellington or in one of its referral regions. As there is no control group, our “usual care” infants with the same risk factors who decline to participate will not be followed and therefore cannot be compared to the PĒPI ARC participants. Economic analysis of the effectiveness of PĒPI ARC for families and the health system will not be conducted.

The study has many strengths. One is the delivery of the Hub using two parts: an MDT face-to-face clinic and a regional virtual approach provides an opportunity to decrease inequitable access to care for local and regional infants and families. Some regional centres may not have the experienced staff to deliver the CPCN Recommendations, and the Hub will support and educate clinicians to ensure regional centres can, over time, deliver the recommended assessments and follow-up. The inclusion of qualitative feedback from both families and health professionals will provide depth of context to our findings.

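### H4's 17% and 34% thresholds come from register figures not shown to match the study's population, era or age scale, and are probably too easy to exceed without any Hub effect

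*Protocol article*

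**What the plan says.** - **Benchmark (Study design and setting).** The figures are introduced with "For the Wellington NICU catchment area". The 6-month figure is given as: "data from the NZ CP Register (2009–2020) showed that 17% of infants received a diagnosis of CP before 6 months of age". The 12-month figure comes from the same source: "and 34% before 12 months (22"). No restriction to NICU-admitted or newborn-risk children is stated, and nothing says whether the ages are corrected for prematurity.
- **Thresholds (Hypotheses, H4).** The 12-month threshold is: "More than 34% of infants with CP will be diagnosed before 12 months of corrected gestation age (CGA"). The 6-month threshold is: ">17% before the age of 6 months CGA".
- **Who is studied.** Infants must be "admitted to the NICU at Wellington Regional Hospital within the study period" and meet the Table 1 risk criteria. The Discussion confirms: "The study is limited to only infants with newborn detectable risk factors for CP who are admitted to the Wellington NICU".
- **Timing of guidance (Introduction).** "In 2017, an international evidenced-based guideline was published for accurate and early CP diagnosis". The national CPCN Recommendations followed in 2020.
- **Comparator (Discussion).** There is no control group, and eligible infants whose families decline are not followed.

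**The concern.** H4 is the hypothesis attached to secondary objective 4i, whether the Hub model lowers the age at CP diagnosis. Without a concurrent control, H4 can be judged numerically only against the two register percentages. That comparison is informative only if those percentages approximate what the same kind of infant would have experienced without the Hub. The document does not show this for population, calendar period or age scale, and it does not list the mismatch as a limitation. If the thresholds are too low for this cohort, H4 can be met with no Hub effect and still be read as evidence of earlier diagnosis.

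**Working it through.** **1. Do the thresholds match the source?** Yes. The register values, 17% and 34%, are the H4 values, 17% and 34%. They are carried over without adjustment.

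**2. The two sides compared.**

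| | Register figures | H4 cohort |
|---|---|---|
| Population | Described by geographic catchment only | Wellington NICU admissions meeting Table 1 |
| Period | 2009–2020 | Study runs March 2023 to September 2024 |
| Age | Months of age, correction not stated | Corrected age |

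**3. Population.** The Introduction says that infants with detectable newborn risks can be diagnosed from 3 months corrected, and that CP has historically been diagnosed on signs that often appear later. The usual-care sections show that high-risk NICU infants already receive neonatal therapist referral and developmental follow-up. Three regional centres have GMA-trained clinicians, three more send videos to Wellington, and every region has HINE-trained therapists. Such infants would probably be diagnosed earlier than a mixed catchment population.

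Illustration, with assumed inputs that are not in the document. Let *s* be the newborn-risk share of register cases, and let newborn-risk infants be *r* times as likely as the others to be diagnosed early. With register proportion *B*, the newborn-risk proportion is *r·B / (s·r + 1 − s)*.
- *s* = 0.7, *r* = 1.5: at 12 months 1.5 × 0.34 / 1.35 = 38%; at 6 months 1.5 × 0.17 / 1.35 = 19%.
- *s* = 0.4, *r* = 3: at 12 months 3 × 0.34 / 1.8 = 57%; at 6 months 3 × 0.17 / 1.8 = 28%.
- *r* = 1: 34% and 17%, so no bias.

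**4. Era.** Of the 12 register years, 8 (2009–2016) precede 2017 and 11 (2009–2019) precede 2020. The document does not say whether these are birth or diagnosis years. Usual-care staff are said to be trying to implement the CPCN Recommendations already. The Introduction cites clinics where the average age at diagnosis fell after the guideline was implemented (18 to 12 months; 19.5 to 9.5 months). Some improvement since the register period is therefore plausible without the Hub.

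**5. Age scale, only if register ages are uncorrected.** Offset = (40 − gestation in weeks) × 7 / 30.44 months.
- 26 weeks: 14 × 7 / 30.44 = 3.2 months, so 12 months corrected is 15.2 months chronological.
- 32 weeks: 8 × 7 / 30.44 = 1.8 months.
- 40 weeks: 0.

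At 26 weeks, linear interpolation between the two register points gives 17 + 3.22 × (17/6) = 26% by 6 months corrected. Beyond 12 months the register gives no slope. The national figures in the Introduction (about 40% by 12 months, 50% by 17) give 2 points per month, hence 34 + 3.22 × 2 = 40%. Extending the register's own 6-to-12-month slope gives 34 + 3.22 × (17/6) = 43%.

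**6. Consequence.** Assume 12 CP cases (10% of the 120 anticipated infants; the 10% is an assumption). Four of 12 is 33.3%, so the 12-month part of H4 needs at least 5. Two of 12 is 16.7%, so the 6-month part needs at least 3. Binomial probability of exceeding the threshold with no Hub effect:

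| True rate by 12 months | 34% | 40% | 45% | 50% |
|---|---|---|---|---|
| 12 cases, ≥5 | 39% | 56% | 70% | 81% |
| 18 cases, ≥7 | 41% | 63% | 77% | 88% |

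At 6 months with 12 cases, the probability is 33% if the true rate is 17%, 51% at 22% and 61% at 25%.

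**The case against.** - **The register's population and age scale are not known to differ.** A reader might infer that the benchmark covers all CP in the catchment. The text does not say so; a NICU-linked extract cannot be excluded, and the cited source is not available here. A reader might likewise infer uncorrected ages. But the Abstract writes three months of age for what the Introduction gives as 3 months corrected, so the article uses the phrase loosely. This stands: the age component is conditional, and the population component rests on the absence of a stated restriction.
- **The 26-week example is near the extreme.** Table 1 also admits infants up to term, for instance with HIE or stroke, for whom the shift is small or nil. The gestation mix is not given, so no cohort-level shift can be computed. This stands.
- **Numerical corrections depend on their inputs.** Suppose 40–60% of register cases carried newborn risk and 10–20% of the others were diagnosed before 12 months. The matched figure would then be 43–70%. With an even split and 30% among the others it is (0.34 − 0.5 × 0.30)/0.5 = 38%. Similarly, a 12-month value of 44% at 26 weeks requires joining the catchment's 34% to the national 17-month median, although the national share by 12 months is already about 40%. None of these is an estimate for this study. This stands.
- **The stakes are limited.** This is half of one secondary objective, labelled limited efficacy, in a feasibility study. Table 4 measures average age at diagnosis, and the analysis section assigns the objective to descriptive statistics. The lack of a control group, the restricted population and possible changes in usual care are disclosed, and the Introduction also gives a national median as context. This lowers the severity. It does not remove the point, because H4 still fixes numerical thresholds and none of the disclosures is linked to their validity.

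**Conclusion.** The point holds in a limited form and should be addressed. H4's thresholds come from register figures described only by catchment, for 2009–2020, and are applied to a NICU-admitted, newborn-risk cohort in 2023–2024 on a corrected-age scale. The population and era differences probably make the thresholds too easy to exceed. The population part assumes that the register figures were not restricted to similar infants; the era part assumes that usual care has improved since. The age-scale part applies only if register ages are uncorrected, and only to preterm infants. The size of the bias cannot be fixed from the document, and all the percentages above are illustrative.

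A reader might conclude that three established mismatches all favour the Hub by a known amount. The document supports a probable direction for two, a conditional one for the third, and no amount. A reader might also infer that a matched benchmark would allow a result above threshold to be credited to the Hub. It would not: that limit belongs to any uncontrolled design.

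**What to change.** Before analysis:

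1. State what the register figures cover: which children, whether 2009–2020 refers to birth or diagnosis years, and whether ages are corrected.
2. If the register holds the needed fields, re-extract the proportions for NICU-admitted children meeting Table 1, from recent birth years and in corrected age. Use those figures, with 95% CIs, in H4.
3. If this cannot be done, drop 17% and 34% as a test, report age at diagnosis descriptively with the register figures as context, and do not claim that the Hub reduced age at diagnosis.
4. In either case, add the benchmark's comparability to the limitations and avoid causal wording.

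The cost is one register query and a wording change to H4, with the matching ethics amendment and registry update. Nothing in the document shows that the register records NICU admission or Table 1 criteria, so step 2 may prove impossible. A matched benchmark will probably be higher and less precise, because it rests on fewer children. Enrolment, intervention and study data collection are unchanged.

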### Patient and public involvement

The development and refinement of the study question, study protocol, Hub design, and resources were guided by three working groups: whānau Hui, the advisory group (provided local and cultural advice), and the steering group. A specific focus was placed on the voices of Māori and Pasifika whānau, who are reported to have higher rates of preterm birth (23) and poorer preterm outcomes (24). In the planning stages of PĒPI ARC, whānau hui (meetings/gatherings with family members of infants who had been admitted to the NICU) involved focused discussions about their Wellington NICU experience, reflections on their journey, use of assessment tools, and possible improvements. Families were informed about the study design in the following areas:
•Early diagnosis conversations and information sharing—consistent, timely, honest, and appropriate•Service delivery: the experience of early diagnostic assessments in NICU and within the community service•Hearing the voice of the parent•Hub design•Cultural needs and safetyThe PĒPI ARC advisory group consisted of families and health professionals including a Māori researcher and advisor to support our commitment to Te Tiriti O Waitangi and equitable health outcomes for Māori and a Pasifika social worker. The PĒPI ARC steering group, formed by experts in early detection of CP from NZ and Australia, guided the planning and provided ongoing oversight of the study.

### Participants and recruitment

Participants for this study will be formed by two groups, namely, the infants and their parent/caregivers, and the health professionals involved/interacting with the PĒPI ARC Hub. There are no limits placed on the sample size, and a formal sample size calculation is not required. Based on the historical figures of the number of infants admitted to the NICU at the Wellington Regional Hospital and infants aged <28 weeks, up to 120 infants are anticipated to meet the study eligibility during the 12-month recruitment period. There will be no restrictions on other care or interventions partaken in by participants.

#### Infants and parents/caregivers

Infants must meet the following eligibility criteria:
i.admitted to the NICU at Wellington Regional Hospital within the study period,ii.have a discharge address located within the Wellington region or within one of the referral regions of the Wellington NICU, andiii.and meet the criteria of the CPCN Recommendations for newborn detectable risks for CP (Table 1).Infants will be excluded if they are born with a life-limiting condition and not expected to survive past the first year of life or if the family is expected to move out of the catchment area before the infant is 3 months CGA.

Infants and their parents/caregivers will be invited to participate in the study by a member of the PĒPI ARC research team (not directly involved in providing healthcare for the infant in the NICU). Recruitment can occur at any point during the NICU admission prior to discharge. Support from social workers and Whānau Care Services is available to assist with recruitment decision-making, and parents are encouraged to discuss and seek support from their extended family. Families will be advised that they can instead choose the usual care option (see below).

#### Health professionals

All health professionals who engage with the PĒPI ARC Hub will be invited to complete a questionnaire about their experience and acceptability of the PĒPI ARC model of care. There are no exclusion criteria. Health professionals will be invited to complete a semi-structured interview about their experiences and acceptability of the PĒPI ARC Hub.

The members of the PĒPI ARC team will complete a team-specific questionnaire focused on the acceptability of PĒPI ARC.

### Intervention—while in the NICU

#### All infants enrolled in PĒPI ARC

All families will receive:
•*Welcome folder* with information about the study and the PĒPI ARC team and documents to help them navigate their NICU journey and transfer to a regional centre or discharge home with community follow-up. They will also be provided with education and instructions on filming and transferring GMA videos to the PĒPI ARC team after discharge.•*PĒPI passport* aimed to improve health literacy, support a relationship model of care in the NICU, allow families to share neurodevelopmental information about their infant with different healthcare providers after discharge from NICU, and help smooth the transition from the NICU to regional centres.The passport was developed in partnership with the health professionals and families and includes both English and Te Reo Māori translations. Families can document the developmental strengths and challenges, completed assessments and results, and plan for medical and developmental follow-up of their infants.

#### Infants and families living in the regional referral areas

A PĒPI ARC research nurse will support out-of-region families throughout their NICU journey, upon discharge/transfer, and follow up with the regional services to provide continuity of care as part of the “one-stop shop”. Infants from Wellington will be supported by the discharge facilitator team as part of NICU usual care.

### Intervention—after discharge from the NICU

#### Infants and families living within the Wellington region

##### Face-to-face clinic

A face-to-face MDT clinic appointment (lasting 90 min) will take place in a community setting when the infant is between 12 and 16 weeks CGA. This Hub appointment will replace their usual care appointment with their hospital neonatologist at the same age. The MDT will consist of a neonatologist or developmental paediatrician, a GMA and HINE-trained therapist, a social worker, and a clinic nurse and may also include assessments by a speech and language therapist (SLT)/dietician if clinically indicated.

The infant will have a growth, development, medical, and social work assessment, and will be evaluated using the Feeding Matters Infant and Child Feeding Questionnaire (ICFQ) (25). Any previously collected neuroimaging and GMA will be reviewed, and a GMA and HINE (recording scores and number of asymmetries) will be performed (Table 2). The family will also have time with the social worker in private. Assessment findings, resources, and support will be shared with the family as part of the appointment (as outlined in Table 3) and with the local healthcare providers of the infant via an electronic assessment report. Both the family and health provider will also receive a detailed clinic letter within 2 weeks.

**Table 2 T2:** PĒPI ARC clinic assessment schedule (12–14 weeks CGA).

Assessment	Schedule	Trigger for second clinic visit/referrals
Neuroimaging head ultrasound/MRI	Review of prior neuroimaging and need for further imaging assessed.	Referral for MRI (if not already obtained) if: • Abnormal/absent GMA and/or • HINE score < 57, and assessed at high-risk of CP
GMA	• General Movements Assessment of presence or absence of normal fidgety movements. • Review of video captured by parents/caregivers prior to clinic, or video taken at clinic visit^a^	Repeated 2 weeks later if abnormal/absent
HINE	• 3 months Hammersmith Infant Neurological Examination	Recommended to repeat at 6 months CGA if GMA and HINE assessments are incongruent.
ICFQ (25)	• Completed by the family before or at the clinic appointment	Referral to speech and language therapist (SLT) and/or dietician will be made (if not already involved) if two or more questions indicate red flags for feeding difficulties (25)

MRI, Magnetic Resonance Imaging; GMA, General Movements Assessment; HINE, Hammersmith Infant Neurological Examination; CP, cerebral palsy; CGA, corrected gestational age; ICFQ, The Feeding Matters Infant and Child Feeding Questionnaire.

^a^
Scored by the GMA team or at least two senior assessors (inter-rater reliability of the assessors will be established beyond 80% prior to PĒPI ARC clinic appointments beginning). If consensus on scoring is not reached, the GMA will be reviewed independently by a third assessor, including referral to expert assessors if needed until consensus is reached.

**Table 3 T3:** Process plan for communicating outcomes to families/health professionals.

If an infant is assessed to be at low risk of CP: • Verbal and written feedback will be provided to the family and local team. • The infant will be discharged from the PĒPI ARC clinic to usual care.
If the assessments are inconclusive: • Explanation of inconclusive findings will be provided verbally and documented in clinic letters provided to the family and neonatologist/therapist. • The infant will be seen in the PĒPI ARC clinic for further assessment in 2–4 weeks for a repeat clinical examination.
If an infant is diagnosed with CP or high-risk of CP: • The family will be offered a follow-up appointment with the PĒPI ARC team including the social worker within 1–2 weeks’ time (face to face or telehealth based on their preference) to answer any questions and receive more information. All ongoing care will be with their local neonatologist/paediatrician and therapist. • Screening for comorbidities will occur, and genetic testing will be offered. Support and follow-up referral will be made. • Information about the diagnosis of high-risk of CP or CP, the referrals made, and advice about ongoing follow-up and monitoring will be provided to the family of the infant, primary neonatologist/paediatrician, therapist, and GP.

CP, cerebral palsy; GP, general practitioner.

